## Abstract

Cancer-related financial hardship (i.e., financial toxicity) has been associated with anxiety and depression, greater pain and symptom burden, treatment nonadherence, and mortality. Out-of-pocket healthcare costs and lost income are primary drivers of financial toxicity, however, income loss is a pronounced risk factor for cancer patients with low incomes. There has been little progress in developing an income intervention to alleviate financial toxicity cancer patients with low incomes. Unconditional cash transfers (UCT), or guaranteed income, have produced positive health effects in experiments with general low-income populations, but have not yet been evaluated in people with cancer. The Guaranteed Income and Financial Treatment (GIFT) Trial will use a two-arm randomized controlled trial to compare the efficacy of a 12-month UCT intervention providing $1000/month to treatment as usual on financial toxicity, health-related quality of life and treatment adherence in people with cancer who have low-incomes. The study will recruit 250 Medicaid beneficiaries with advanced cancer from two comprehensive cancer centers in Philadelphia, obtain informed consent, and randomize patients to one of two conditions: (1) $1,000/month UCT or (2) treatment as usual. Both arms will receive information on financial toxicity and the contact information for their hospital social worker or financial advocate upon enrollment. Participants will complete online surveys at baseline, 3, 6, 9, and 12 months from enrollment to collect patient-reported data on primary (i.e., financial toxicity, health-related quality of life, and treatment adherence) and secondary outcomes (i.e., anxiety, depression, food insecurity, housing stability). Social security records will be used to explore the effect on mortality at 2, 3, and 5 years post-enrollment. Linear mixed-models will be used to analyze all primary and secondary continuous outcomes over time and general estimating equations with a logit link and binary distribution for all binary outcomes over time. Differences between treatment and control groups and treatment effects will be determined using models that control for age, gender, race, baseline food security, baseline housing stability, and baseline ECOG. Findings from this study will have significant implications for the development and implementation of programs and policies that address the financial burden of cancer and other serious illnesses.

## Introduction

### Background and rationale

At least one-in-three cancer patients experience cancer-related financial hardship during the course of their treatment (Yabroff et al., 2018). Cancer-related financial hardship has been associated with anxiety and depression, greater pain and symptom burden, and treatment nonadherence (Zullig et al., 2013; Delgado-Guay et al., 2015; Arastu et al., 2018). Cancer patients are at a high risk for bankruptcy, an event that has been linked to a threefold increase in the likelihood of early mortality (Ramsey et al., 2013, 2016). The adverse health effects associated with cancer-related financial hardship are called *financial* toxicity. Financial toxicity has been identified across the socioeconomic spectrum of cancer patients, but women, people of color, and low-income families experience financial hardship more often and with greater severity (Altice et al., 2016; Tucker-Seeley and Yabroff, 2016). High out-of-pocket healthcare costs and lost income are the primary drivers of financial hardship in the general cancer-affected population (Yabroff et al., 2018). However, income loss is a pronounced risk factor for low-wage workers who tend to work in sectors that lack adequate employment and income protection programs during periods of disability (Blinder et al., 2017; Blinder and Gany, 2020). As a result, cancer patients with low incomes are at greater risk of food and housing insecurity (Gany et al., 2021). Conditions of material deprivation, one domain of the social determinants of health, are robustly associated with a host of adverse health outcomes and are a critical driver of cancer health disparities (Coughlin, 2021).

The impact of financial toxicity has been well documented, however there has been little progress in developing an intervention robust enough to alleviate financial toxicity patients with cancer (Doherty et al., 2021; Offodile et al., 2022). Studies suggest that, by improving access to copayment assistance programs and optimizing insurance, financial navigation can reduce out-of-pocket costs, but treatment effects are small to moderate and programs are underutilized due to patient- and system-level factors (Shankaran et al., 2018; Yezefski et al., 2018; Monak et al., 2019; Watabayashi et al., 2020; Wheeler et al., 2020; de Moor et al., 2021; McLouth et al., 2021; Biddell et al., 2022; Smith et al., 2022). In addition to individual-level support interventions like financial navigation, experts suggest that structural, policy-level solutions are needed to mitigate the economic burden of illness in the U.S (Yabroff et al., 2020). Unconditional cash transfers (UCT), sometimes described as *guaranteed income*, have produced positive health effects in experiments with general low-income populations, but have not yet been evaluated in people with cancer who have low incomes (Gibson et al., 2018). The Guaranteed Income and Financial Treatment (GIFT) Trial will use a two-arm randomized controlled trial design to compare the effectiveness of a monthly $1,000 UCT to treatment as usual on financial toxicity, health-related quality of life and treatment adherence in people with cancer who have low incomes.

The study was funded by the One Family Foundation and the Independence Blue Cross Foundation as the Institute for Health Equity's inaugural project. Our UCT intervention stands out for its unique feature of including a waiver that allows Supplemental Security Income (SSI) recipients to receive cash assistance without jeopardizing their existing benefits. We secured this waiver through a cooperative agreement with the Social Security Administration (SSA). This waiver is necessary because cash payments count as income under the SSA rules, which can affect a recipient's eligibility for SSI benefits. SSA defines income as anything a person receives during a calendar month that can be used to fulfill their needs, whether in cash or in-kind, such as food or shelter (Social Security Administration, 2023). This waiver is a crucial component of our program as it enables SSI recipients to participate in the program without fear of losing their existing benefits. Without the waiver, our program would not be accessible to the individuals it aims to support, and its impact would be significantly limited. SSA will notify local Social Security offices that the individual is participating in an ICAP study that allows them to receive an additional $1,000 per month for 12 months.

#### Choice of comparator

In spite of growing awareness of the health effects of financial toxicity, clinical practice is widely dependent on a passive intervention model that requires patients to self-report financial and social needs (McLouth et al., 2021). Social workers and financial advocates who can help patients access copayment assistance, community grant programs, and public benefits are the standard of care. Participants in both arms of the study will receive information on financial toxicity and the contact information for their hospital social work and financial advocacy departments.

#### Research hypothesis

A monthly UCT of $1,000 for 12 months is more effective than treatment as usual in the prevention of financial toxicity, diminished quality of life, and treatment nonadherence in people with cancer who have low incomes. See Figure 1 for the GIFT Trial causal model.

**Figure 1 F1:**
[figure not shown]
GIFT Trial causal model depicts the causal model underlying the GIFT Trial in which UCT impacts financial toxicity, health-related quality of life, treatment adherence, anxiety, depression, food, and housing instability and mortality.

#### Study objectives

##### Primary objective

To determine if a monthly UCT of $1,000 for 12 months is more effective than treatment as usual on financial toxicity, health-related quality of life, and treatment nonadherence in people with advanced cancer (as determined by cancer stage and ECOG status) who have low income (as determined by Medicaid status).

##### Secondary objectives

To determine if monthly UCT is more effective than treatment as usual in reducing anxiety, depression, and poverty exposures (i.e., food and housing insecurity).

##### Exploratory objective

To compare the monthly UCT to treatment as usual with regard to mortality in people with cancer who have low incomes.

#### Trial design

The GIFT Trial is designed as a randomized, controlled, unblinded, multicenter superiority trial with two parallel groups and a combined primary endpoint of financial toxicity, quality of life, and treatment adherence. Randomization will be performed as block randomization with a 1:1.5 allocation stratified by age and treatment center.

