### Outcomes

#### Primary outcome measures

The primary outcomes of interest are financial toxicity, quality of life, and treatment adherence. Primary outcomes will be measured at baseline, 3, 6, 9, and 12 months.

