#### Power analysis for primary outcomes

All power calculations were conducted in Power Analysis and Sample Size (PASS) 2023. Power was calculated at alpha=0.05 with 200 patients at five timepoints. For all power estimates, we assumed an 8% mortality rate between primary timepoints; therefore, 28% of patients will be deceased by the 12 month time point (American Cancer Society, 2019). Power calculations were conducted with missing timepoints rather than on imputed data since we plan to compare imputed to non-imputed models. We further assumed an exchangeable correlation structure with a moderately strong intraclass correlation (r = 0.6).

Many estimates were obtained through the pilot analysis. We conducted an observational, pre-test/post-test pilot study in which we recruited 150 financially burdened cancer patients and provided them with a one-time grant of $1,000. We measured primary and secondary outcomes of interest prior to the intervention delivery and two months after to examine changes over time. We expect that the full trial, which will provide participants with 12 times the amount of cash that was provided in pilot, will yield higher treatment effects. We believe the estimates from the pilot are conservative estimates for the full trial, and any estimates not obtained from the pilot were overly conservative to ensure full power.

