##### Quality of life

The pilot analysis saw a mean SF-36 aggregate score difference of 3.4 units (Treatment = 39.8, control = 36.4) and an overall standard deviation of 29.4 units. We expect the covariates we control for in the linear mixed model to have a moderate to moderately strong correlation (between 0.5 and 0.8). Although we expect to observe a larger mean SF-36 aggregate score difference in the full trial, we calculate the power of our full trial to be between 0.1831 and 0.3294. In order to be fully powered, we will need to observe a mean SF-36 aggregate score difference of at least 6.5 assuming similar standard deviations. Although this is 2.9 units larger than observed in the pilot, we expect to see a larger difference between the treatment and control groups because of the compounding effect of monthly UCT relative to treatment as usual.

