##### Treatment nonadherence

The pilot analysis saw a mean 30-day nonadherence rate of 11.5% for the control group and a mean nonadherence of 14.7% for the treatment group. We did not expect to observe an increase in nonadherence from pre to post intervention and do not have sound evidence to explain it. However, we can infer that because we only provided the pilot group with a one-time payment of $1,000, that this amount was insufficient to produce changes in 30-day nonadherence. Although we do not have sufficient evidence to corroborate nonadherence rates for our treatment group, we found the nonadherence rate for our control group to be somewhat lower than previous research on nonadherence in financially burdened cancer patients (Zullig et al., 2013; Costas-Muniz et al., 2016; Lee and Khan, 2016; Lee and Salloum, 2016; Nipp et al., 2016; Knight et al., 2018; Zhao et al., 2019). Two past studies that focused on reducing nonadherence to chemotherapy using a behavioral intervention to improve quality of life found significantly lower nonadherence to chemotherapy rates in the intervention group (19%) than in the control group (62.5%) (Cheville et al., 2015). We expect the covariates we control for in the GEE model to have a moderate to moderately strong correlation (between 0.5 and 0.8). Thus, we calculate the power to detect any difference between the treatment and control group to be between 0.065 and 0.095. If the nonadherence rate for our the trial treatment group is similar to the pilot, we will need to observe a nonadherence for the control group to be at least 32% which is possible given the nonadherence rates observed in past studies.

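### The Trial design section announces a combined primary endpoint, but the protocol lists, models and powers three separate outcomes and gives no rule for success

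*Protocol article*

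**What the plan says.** The Trial design section describes a superiority trial with "a combined primary endpoint of financial toxicity, quality of life, and treatment adherence". The section on primary outcome measures uses the plural instead: "The primary outcomes of interest are financial toxicity, quality of life, and treatment adherence". The research hypothesis and the primary objective join the three with *and*, and do not say how they combine.

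The Statistical methods section assigns linear mixed models to continuous outcomes and GEE with a logit link to binary ones, so the three outcomes go into separate models. It describes no composite score, global test, ordering or division of alpha.

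The power section treats each outcome alone. Its common basis is "Power was calculated at alpha=0.05 with 200 patients at five timepoints". COST has a stated power of 0.867 to 0.993. For quality of life, "we calculate the power of our full trial to be between 0.1831 and 0.3294". For nonadherence, "we calculate the power to detect any difference between the treatment and control group to be between 0.065 and 0.095". No power is given for anything combined.

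**The concern.** A reader of the Trial design section expects one primary test. A reader of the later sections finds three, with nothing to say whether one win is enough or all three are needed. The two readings agree when all three outcomes succeed or none does. They disagree when results are mixed, and on the protocol's own powers a mixed result is the likeliest. The most probable pattern is COST significant and the other two not: a positive trial under an *any* rule and a negative one under an *all* rule. The trial is unblinded and its primary outcomes are self-reported, so a rule chosen after the data are seen would be hard to defend.

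**Working it through.** **Inputs from the protocol article.** Alpha 0.05 and 200 patients (power section; sidedness not stated, two-sided assumed). Allocation by "block randomization with a 1:1.5 allocation stratified by age and treatment center", hence 80 and 120 of 200. Deaths: "we assumed an 8% mortality rate between primary timepoints; therefore, 28% of patients will be deceased by the 12 month time point" (1 − 0.92^4 = 28.4%). Exchangeable correlation 0.6. Covariate correlation r of 0.5 to 0.8. Pilot effects: COST 2.4 (SD 7.1); SF-36 aggregate 3.4 (SD 29.4); nonadherence 14.7% treatment and 11.5% control.

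**Step 1: reproduce the stated powers.** With m post-baseline visits observed, a patient contributes m / (1 + 0.6(m − 1)) units of information. Averaged over the four visits with 8% loss per interval, this is 1.267. Effective sizes are 80 × 1.267 = 101.3 and 120 × 1.267 = 152.0. The residual SD is SD × √(1 − r²).

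- COST, r = 0.5: SD 6.149, SE = 6.149 × √(1/101.3 + 1/152.0) = 0.789, z = 2.4/0.789 = 3.04, power 0.861. For r = 0.8: 0.993. Stated: 0.867–0.993.
- SF-36, same formula: 0.181–0.324. Stated: 0.1831–0.3294.
- Nonadherence, Wald test on the two proportions with the effect scaled by √(1 − r²): 0.072–0.097. Stated: 0.065–0.095.

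All agree within 2 points, so the stated figures can be used as given. They are single-outcome powers at 0.05.

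**Step 2: any one of three at 0.05.** Under independence, 1 − 0.95^3 = 0.143. The ceiling is 3 × 0.05 = 0.15. By simulation with correlated test statistics, the risk is about 12.5% at correlation 0.5 and 10.9% at 0.7. These outcomes are probably positively correlated, so 11–14% is a fair range.

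**Step 3: all three at 0.05.** Joint power cannot exceed the weakest component, 0.065–0.095. Under independence, the lower ends give 0.867 × 0.1831 × 0.065 = 0.010 and the upper ends 0.993 × 0.3294 × 0.095 = 0.031. With test statistics correlated 0.8, simulation gives 0.047 and 0.084.

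**Step 4: the likeliest mixed result.** COST significant and the other two not, under independence: 0.867 × 0.8169 × 0.935 = 0.66 at the lower ends and 0.993 × 0.6706 × 0.905 = 0.60 at the upper ends.

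**Step 5: the hoped-for effects.** The protocol also names an SF-36 difference of 6.5 and a control nonadherence rate of at least 32%. If each gave 80% power, with COST at 0.993, *all three* would have power 0.993 × 0.8 × 0.8 = 0.64 under independence and 0.73 at correlation 0.8. The Step 1 method gives 0.51–0.82 for SF-36 at 6.5 and 0.52–0.83 for 32% against 14.7%, so 80% lies near the top of both ranges.

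**Step 6: cost of an equal split.** The stated COST powers imply z = 1.960 + 1.112 = 3.072 and 1.960 + 2.457 = 4.417. At alpha 0.05/3 = 0.0167 the critical value is 2.394, so power is Φ(0.678) = 0.75 and Φ(2.023) = 0.98.

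**The case against.** The strongest reply is that testing order and alpha division are commonly left to a statistical analysis plan, which is not shown, and that this is a condensed article. That stands for the missing multiplicity rule taken alone. It does not cover the conflict: the protocol makes a positive statement about its primary endpoint that its own outcome, analysis and power sections do not follow, and an analysis plan would not make those sections agree.

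Four stronger readings are tempting, and the document does not support them.

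- *Each outcome will be tested at 0.05.* That level appears only as a power input. The Statistical methods section gives neither a test level nor a sidedness, so the 11–14% is conditional.
- *One win would be reported as a positive trial.* The text states neither an *any* nor an *all* rule. It only fails to exclude either.
- *An all-three rule has at most 9.5% power and is almost certain to fail.* This holds only on pilot-based powers. The protocol calls the pilot estimates conservative, and Step 5 shows how much larger effects would change the answer. In addition, 0.065–0.095 is power for a difference in either direction, computed from a pilot difference that runs against treatment. The chance of a significant result favouring the cash transfer on that component would be only about 0.5–1%. The ceiling is valid, but it mostly reflects the adherence assumption.
- *The false-positive risk is 40%.* That figure (1 − 0.95^10) needs the eight SF-36 subscales to be tested separately and independently. The power section uses a single aggregate, and separate subscale tests are not stated anywhere.

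**Conclusion.** The point holds as an internal contradiction about the primary endpoint, with no stated definition of success. Its size depends on the rule eventually applied. An *any* rule at 0.05 each carries about 11–14% false-positive risk, at least double the nominal level, assuming two-sided tests and correlations between 0 and 0.7. An *all* rule has power no higher than 0.065–0.095 on the pilot-based figures, and roughly 64–73% if the hoped-for effects each gave 80% power. Nothing in the document shows which rule the sponsor intends. It should be settled before outcomes are analysed.

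**What to change.** Delete *combined* from the Trial design section, bring it into line with the section on primary outcome measures, and prespecify one rule that controls error across the three outcomes.

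One workable rule is a fixed sequence at two-sided 0.05: COST first, as the only outcome with pilot-based power above 80%; then one defined quality-of-life score; then adherence. Once a step fails, later outcomes are reported as estimates with intervals. The second step needs a single instrument and score: the text uses SF-36 and defines only eight subscales, the power section uses an undefined aggregate, and Table 1 lists FACT-G.

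The change needs no patients or data, and COST keeps its full 0.05. It has three costs:

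- Quality of life is not confirmatory if COST fails. Adherence is not confirmatory if either earlier step fails; at the stated quality-of-life power, that step alone fails 1 − 0.3294 = 67% to 1 − 0.1831 = 82% of the time.
- The sequence ranks outcomes that the hypothesis and primary objective treat as equal.
- COST becomes the gatekeeper, although the Discussion concedes that its clinically meaningful change is not established and that it has not been validated in this kind of population.

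Holm's procedure avoids the ranking. Its price is COST power of about 0.75–0.98 at the first step, in place of 0.867–0.993.

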## Methods

### Study setting

We selected two large, minority-serving, urban cancer centers to conduct the trial. Abramson Cancer Center at Penn Medicine and Sidney Kimmel Cancer Center at Jefferson Health.

### Eligibility criteria

Patients must provide signed (paper or electronic) informed consent before any study procedures occur. In order to verify patients' low-income status, we use Pennsylvania Medicaid beneficiary status as a proxy variable for eligibility. To be eligible for Pennsylvania Medicaid (i.e., Medical Assistance) individuals must earn <133% of the federal poverty line (FPL) or 250% FPL if considered a “disabled worker” (i.e., less than $39,900 or $75,000/year for a family of four respectively) (Pennsylvania Department of Human Services, 2023; US Centers for Medicare Medicaid Services, 2023). All participants will have household incomes under 250% FPL.

#### Inclusion criteria

Patients eligible for the trial must comply with all the following at randomization:

Age ≥ 18Newly diagnosed or recurrent advanced cancer (Stage 3–4)Receiving chemotherapy or immunotherapy (with or without radiation) at one of the recruitment sitesWithin 12 months of receiving systemic therapy and on surveillance at one of the recruitment sitesECOG performance status of 1–2A Pennsylvania Medicaid beneficiaryA Pennsylvania resident

#### Exclusion criteria

Eligible for hospice (i.e., determined by provider to have a prognosis of 6 months or less) at time of randomizationUnable to communicate in English, Spanish, or Mandarin

### Description of study conditions

#### Intervention arm

The intervention in this trial is a philanthropically funded UCT of $1,000 per month for 12 months. Upon randomization to the intervention arm, people in the intervention arm will be contacted by the guaranteed income (GI) manager who will schedule to meet the participant either in-person at an upcoming cancer center appointment or by Zoom videoconferencing software. At the meeting, the GI manager will explain the UCT intervention in detail, explain how participation may impact public benefits, how specific public benefits will be protected during participation in the trial (i.e., Medicaid, SSI, SSDI, SNAP), and answer questions about public benefit concerns. The GI manager will then provide the participant with a USIO Inc (2023) debit card, in-person or by mail, with instructions on how to use it and the dates that they can expect to receive payment. Each month the debit card will be refilled with $1,000 and participant will receive a confirmation text message or email. Participants will be asked to provide the name and contact information of a household member or caregiver who will serve as a beneficiary for their remaining monthly UCT in the event that they enter a nursing home facility or pass away before the end of 12 months.

